### Theory and content of interventions

Two interventions were compared in this study: PACE, and a culturally enhanced version of PACE: PACE Plus. PACE is based on the Model for Managing Chronic Disease (MMCD) [18]. The theoretical foundation for the MMCD includes principles of self-regulated learning and constructs from social cognitive theory [19-21]. Self-regulatory processes have been shown to have an impact on ability to organize, prioritize, and correct behavior [20]. Social cognitive theory is a particularly appealing basis for these interventions as they address management of a chronic disease, that is, a condition the physician can expect to treat over a long period of time. The theory posits that personal, social, and behavioral influences interact to cause behavior. In the applications of the theory, the physician self-regulates his/her own behavior to better achieve desired responses from the patients: more effective at-home management of the child’s condition, greater adherence to the physician’s recommendations by the family, and greater satisfaction with the physician’s care. The theory and previous work with PACE [13,14,22,23] supports the idea that influence becomes reciprocal. The physician is reinforced by the patient’s positive response and is thus further inclined to collaborate with the patient, communicate more effectively, and improve asthma care. The patient’s behavior is similarly reinforced through satisfaction with the care and results. Theoretically, this cyclical reinforcement over time should lead to stronger and stronger partnerships between family and physician in managing the child’s illness.

#### *PACE*

PACE is targeted to primary care physicians. The MMCD framework informs the intervention components. Physicians make decisions and take action based on previous experience and the consequences they anticipate. When desired consequences are achieved, behavior is reinforced and motivation to use the behavior again increases. This motivation is experienced as an increased sense of self-efficacy or confidence that the behavior can be successfully used again to achieve similar or better results. Learning is enhanced by self-regulation, that is, the learner’s efforts to observe, evaluate, and react to his or her own responses to a problem. A primary channel for learning is observing and drawing conclusions in vicarious situations. Physicians can learn from role models and/or other physicians who have excellent treatment and counseling skills.

PACE consists of two, 2-hour sessions offered to groups of 4 – 6 primary care physicians two weeks apart in an interactive group format. The content of PACE focuses on enhancing communication, therapeutic practice, and the ability of physicians to foster effective management of asthma in their pediatric patients. Since the step-care approach to asthma based on the National Asthma Education Prevention Program (NAEPP) Expert Guidelines for the Diagnosis and Management of Asthma is likely to require a few office visits [8], communication can be accomplished within the framework of these visits. Physicians are therefore provided with an approach in this intervention that can be easily introduced into their ongoing practices, requiring no increases in time and having maximum impact on the patient’s ability to retain and use treatment advice and education.

Table 2 provides an overview of program content for PACE and PACE Plus. Both interventions enable the physician to use a process of self-regulation to improve his/her treatment decisions and counseling via mini-lectures, case studies, videos, and interactive discussion. In PACE, the first segment of the intervention is designed to help physicians to improve their clinical management of asthma through NAEPP protocols for effective treatment [8]. The second segment of the intervention provides the physicians with messages describing strategies to help families manage effectively. The third segment of the intervention teaches physicians techniques that will improve their ability to communicate advice to families, and the fourth segment focuses on up-to-date billing and coding practices for asthma management. The intervention is facilitated by a respected pediatric pulmonologist, primary care physician, and behavioral scientist.

**Table 2 T2:** Comparison of physician interventions

	**PACE**	**PACE PLUS**
** Delivery Format: **	Seminar comprises 2 face-to-face group meetings lasting 2 ½ hrs. each, held over a 2-week period. Format is a combination of mini lecture, video, case studies, & discussion.	Original PACE delivery format with integrated cultural competence skills and components.
** Facilitators: **	Includes an asthma specialist, behavioral science expert, and a primary care physician.	Includes an asthma specialist, behavioral science expert skilled in cross-cultural communication, and a primary care physician.
** Curriculum Components **		
** Clinical aspects of asthma and long-term management **	Trends of asthma in primary care practice	
	Components of good asthma control based on NAEPP Guidelines	
	Written instructions & asthma action plans	
	Review of long-term treatment plan	
	Asthma medications	
	Cases of asthma diagnosis	
** Communication Strategies **	Theoretical background	
	Evidence on asthma medication adherence and from efficacy trial of PACE	
	Video of communication strategies + discussion	
	Introduction of 10 communications strategies	
	Use of self-rating scale and communications strategies with patients between intervention sessions + reflection with group	
** Patient Education Messages **	Video of patient education and presentation of core asthma messages and discussion	Additional discussion questions concerning diverse patient groups specifically African American and Hispanic/Latino pediatric patients and families responding differently to messages
** Cases **	Asthma treatment cases + discussion	Review of case studies highlighting perceptions of treating asthma among patients of African American and Hispanic/Latino race/ethnicity
** Additional Components **	Billing and coding asthma visits	*Cross-cultural communication*
	-review of billing and coding practices for asthma education and counseling via mini-lecture and video. Segment is especially enhanced when facilitated by a billing and coding expert	Review of concerns of African American and Hispanic/Latino patients
		Review of cross cultural communication strategies
		Video highlights cultural issues
		Emphasis on communication barrier being more evident with patients of a different race/ethnicity & means to reduce barriers

#### *PACE plus*

PACE Plus is tailored to cross-cultural communication with a specific focus on working with African American and Latino/Hispanic families. Although it is the same length and intensity as PACE, PACE Plus content differs from PACE in that the billing and coding component is replaced with a mini-lecture segment focused specifically on cross-cultural communication strategies and working effectively with a translator. The content addresses the range of perceptions and experiences of children with asthma and their parents that affect asthma management. This content, gleaned from the literature [24,25] and the clinical experiences of the physician co-investigators, includes topics relevant to the target populations, such as patient perceptions, beliefs, fears, and preferences. Case studies in PACE Plus are embedded in the context of working with African American and Latino/Hispanic patients. The behavioral scientist facilitator in PACE Plus is an individual particularly skilled in cross-cultural communication.

#### *Control condition*

The control condition consisted of usual care. Usual asthma care in the United States recognizes the model of practice as established by National Asthma Education Prevention Program [8]. Participating control physicians acknowledged use of guideline-based care and were unrestricted in their acquisition of updated asthma CME during the study.

### Outcomes and measures

Data are collected from three sources in this study: 1) enrolled physicians complete self-administered surveys, 2) caretakers of patients complete telephone surveys, and 3) health care use data collected via the physician’s office records. Physician and parent/caregiver surveys are completed at baseline, 9 months following the intervention, and 21 months following the intervention. All physician surveys are collected via Qualtrics, an online survey program, or on paper and then returned to the research staff. Following completion of the baseline survey, physicians were randomized and notified of their assignment with further instructions for those randomized to the PACE or PACE Plus arms. Data are collected from parents/caretakers via telephone interviews with trained research assistants. Data are then entered twice into Qualtrics to ensure accuracy.

The primary study outcome is *children’s health care use for asthma*. This includes the number of asthma-related emergency department visits, overnight hospitalizations, and urgent office visits. These measures are collected via self-report during the telephone interviews, and verified using medical records from the physician offices.

Other outcomes of interest include the following:

*Clinical practices of the clinician:* Physician’s self-reported clinical practices. These questions focus on time spent with patients of different duration of care and asthma severity, as well as communication and counseling behaviors. Practice of communication and counseling is measured using the Teaching and Communication Behavior scale [26] which address the frequency, perceived helpfulness, and confidence with which the physician performs different communication strategies.

*Knowledge and use of NAEPP guidelines:* Physician’s knowledge and familiarity with the NAEPP guidelines for asthma management and diagnosis, and their use of NAEPP recommended therapies.

*Cultural competency:* Physician’s use of recommended cultural competence behaviors as well as expectations about their effect and confidence to employ them.

*Asthma symptoms:* Collected from the parent using items based on NAEPP guidelines to measure the intensity and level of symptoms.

*Asthma Control Test:* The validated 5-item Asthma Control Test (ACT) and children’s 7-item ACT measure the effect of asthma on daily functioning, shortness of breath, nighttime and daytime asthma symptoms, rescue medication use, and overall parent-rated asthma control [27].

*Parent/caretaker satisfaction with physician performance:* These items were previously developed by the authors [13] tapping into measure physician performance regarding communication and counseling, and specific facets of general satisfaction with care. Parents/caretaker's views of the physician’s cultural competence is assessed using items based on cross-cultural communication training provided in the PACE Plus training.

*Quality of life*: The 13-item Pediatric Asthma Caregiver’s Quality of Life scale measures limitations, anxieties, and fears caregivers experience due to their child’s asthma [28].

Data are also collected in the physician survey on a wide variety of socio-demographic information, including practice arrangements, professional activities and previous involvement in cross-cultural communication training. Socio-demographic information related to the parent and child was also collected including availability of health insurance.

### Analysis

Analyses will involve both discrete (dichotomous, counts, ordinal) and continuous (measurable) variables. Analysis techniques utilized will be based on the type of variables, categorical or continuous. Initially, descriptive statistics for the characteristics of the sample for each group will be produced. Then t tests/Wilcoxon rank test, chi-squared tests and Fisher’s exact test will be used to detect potential differences on demographic and practice variables between three randomized groups. If differences are found, adjustments in post-test measures, via subgroup and covariance analyses, will be made. Adjusted comparisons, controlling for variables that relate to the outcome will be performed using multivariate regression techniques. Adjusting for variables that relate to the outcome will increase the efficiency of the estimates by reducing the residual error, and correct for bias due to association between drop outs and these variables.

Separate analyses of physicians’ characteristics related to each of the communication and cultural competence skills will be conducted. Multiple logistic regression will be used for dichotomous variables in each analysis with group assignment as an independent variable. Changes in the physicians’ use of specific NAEPP recommended therapies will be examined through logistic regression.

Analyses of the parent interview data will be conducted to assess outcomes that are related to four categories of variables: 1) changes in the child’s health care use for asthma 2) changes in the child’s symptom status 3) changes in parents’ views of physician performance; and 4) increase in asthma-related quality of life for parents. For changes in parents’ views of physician counseling, multiple logistic regression will be used for each analysis with group assignment as an independent variable. The role of patient age and gender, severity of illness, tobacco exposure (as this is associated with increased asthma symptoms), patient insurance (private, Medicaid, or self-pay status), and other relevant influences will be identified for appropriate inclusion in models.

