### Randomization

#### *Experimental design and randomization*

A randomized controlled design was used in this study. At the beginning of the study, a permuted block randomization schedule was created using the RAN TBL and RANUNI functions in SAS to generate blocks of two for random assignment of physicians. Data are collected from three sites, Atlanta, Georgia, New York City, New York, and cities throughout Michigan. It is recognized that geographic site as well as size of practice of the physicians selected for study could impact on results. Thus, randomization was stratified by geographic area (three levels, Atlanta area, metropolitan New York, and Michigan) and size of practice (two levels, solo practice and multiple-physician practices). This randomization ensured that each type of practice and geographic area would be evenly distributed across the three arms of the study, which reduces bias due to these potentially confounding factors in the comparative analysis. Once physicians consented to participate, they were placed into one of the three arms of the study according to the randomization schedule with 44 physicians assigned to PACE, 36 to PACE PLUS and 32 to control (see sample size determination) with a total of 112 physicians and 1062 patients following those physicians into randomization.

Because this evaluation is being conducted for the purpose of recommending interventions for adoption, considerations about external validity of the results are important. One strength of this sample is that it includes physicians from practices in three large metropolitan areas. Thus, although the physician sample involved is not drawn from the entire U.S. population of clinicians, the study results will be somewhat representative of a wide variety of practice sites. Further, because background and practice characteristics of participating physicians will be assessed, it will be possible to make comparisons to the broader group of clinicians practicing in the U.S., as well as judgments about the extent to which the interventions are influenced by these characteristics.

Another threat to external validity, multiple–treatment interference, will be addressed by questionnaire items that will allow us to measure whether physicians have been involved in any other professional education efforts focusing on asthma care and education and cross-cultural communication training.

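### Adjustment is partly triggered by baseline significance tests between randomised arms, and neither the stratification factors nor the baseline outcomes are named as model terms

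*Protocol article*

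**What the plan says.** All of the following is in the protocol article.

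- **Baseline tests.** In Analysis, a set of two-sample and contingency-table tests "will be used to detect potential differences on demographic and practice variables between three randomized groups".
- **Consequence of those tests.** The next sentence reads: "If differences are found, adjustments in post-test measures, via subgroup and covariance analyses, will be made".
- **A second route, with no condition attached.** "Adjusted comparisons, controlling for variables that relate to the outcome will be performed using multivariate regression techniques". The stated reason is that "Adjusting for variables that relate to the outcome will increase the efficiency of the estimates by reducing the residual error".
- **Candidate covariates for the parent-interview outcomes.** "The role of patient age and gender, severity of illness, tobacco exposure" and insurance status are listed, "and other relevant influences will be identified for appropriate inclusion in models".
- **Description of the outcomes.** Health care use is listed as a change, followed by "2) changes in the child’s symptom status 3) changes in parents’ views of physician performance; and 4) increase in asthma-related quality of life for parents".
- **Design factors.** Experimental design and randomization states that "randomization was stratified by geographic area (three levels, Atlanta area, metropolitan New York, and Michigan) and size of practice", with two levels for practice size, because the authors expect both factors could influence the results.

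Outcomes and measures has physician and parent surveys at baseline and at 9 and 21 months after the intervention, so baseline values of the survey outcomes exist.

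**The concern.** After a sound randomisation, any baseline difference between arms is due to chance. A significance test of that difference does not show whether the variable predicts the outcome, and prognostic strength is what makes adjustment worthwhile. A rule that adjusts when a test is significant can therefore bring in irrelevant variables, and the model for the treatment effect is not known until the data are seen. Naming subgroup analysis as a remedy adds to the problem: it estimates effects within parts of the sample and does not correct a comparison of whole arms.

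The second route has a sound aim, but its variables are also still to be identified, and nothing says how the two routes combine. Several versions of each treatment effect are then possible, for two comparisons (PACE Plus with PACE, PACE with control) and several outcomes. Meanwhile the terms with the clearest claim to a place in every model, the two stratification factors and the baseline value of the outcome, are not named.

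**Working it through.** The article gives no figure on this point, so there is none to reproduce. The sample-size figures neither support nor weaken it. Every input marked as assumed is not in the documents.

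**1. How often chance alone triggers the rule.** Assume *k* independent baseline tests, each at 5%, under correct randomisation. The chance of at least one significant result is 1 − 0.95^k.

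| k (assumed) | Chance of at least one difference |
|---|---|
| 5 | 0.23 |
| 10 | 0.40 |
| 15 | 0.54 |
| 20 | 0.64 |

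This counts one test per variable. The t test and the Wilcoxon rank test compare two groups, so with three arms the continuous variables would need up to three pairwise tests each, which raises the chance.

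**2. Named covariates beside design factors.** Named: age, gender, severity, tobacco exposure, insurance, plus an open category. Stratified on: area (3 levels) and practice size (2 levels), so 3 × 2 = 6 strata. Neither factor is on the named list. Practice variables are among those tested at baseline, so practice size could enter if it tested as different, or either factor could enter through the open category. Entry is possible but not fixed.

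**3. If the strata are left out.** Suppose arms are balanced within strata and the strata explain a share R² of the variance between physicians. The true variance of the arm difference is then proportional to 1 − R², while the variance estimated without strata is roughly proportional to 1. The actual test size is about P(|Z| > 1.96/√(1 − R²)). For R² = 0.10 the threshold is 1.96/0.949 = 2.07, giving about 0.039. A simulation of 20,000 trials (two arms of 36 physicians, six equal balanced strata, normal physician-level outcome, all assumed) gives:

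| R² (assumed) | Size, strata omitted | Size, strata included |
|---|---|---|
| 0.05 | 0.043 | 0.048 |
| 0.10 | 0.038 | 0.050 |
| 0.20 | 0.029 | 0.051 |
| 0.30 | 0.021 | 0.051 |

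The error is conservative: standard errors are too large and power is lost.

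**4. If the baseline value is left out.** For a continuous outcome with equal variances at both times (set to 1) and baseline-to-follow-up correlation r (assumed), the variance is 1 for follow-up alone, 2(1 − r) for an unadjusted change score, and 1 − r² with baseline adjustment.

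| r | Adjusted / follow-up alone = 1 − r² | Adjusted / change score = (1 + r)/2 |
|---|---|---|
| 0.3 | 0.91 | 0.65 |
| 0.5 | 0.75 | 0.75 |
| 0.7 | 0.51 | 0.85 |

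These ratios do not carry over to the proportion with an ED visit or to visit counts.

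**The case against.** The strongest reply is that the rule is not the whole plan. The sentence after it commits, without condition, to adjusting for outcome-related variables in order to reduce residual error. That is correct practice, so a reader who infers that adjustment happens only when a baseline test is significant goes beyond the text. This stands, and it weakens any general charge that the plan discards precision. It does not remove the test-triggered rule that sits beside it.

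Second, this is a condensed article, and full lists of model terms are commonly left to the analysis plan. A reader might infer that area and practice size are excluded from the models. The article does not say so, and its covariate list is open. This also stands: the point is only that they are not named, while a data-dependent rule is.

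Third, a reader might take the references to changes as a plan to analyse change scores, and so claim a 25% to 35% variance saving from baseline adjustment (r = 0.5 to 0.3). No change-score model is specified, and the quoted rule itself speaks of covariance analysis of post-test measures. The saving is conditional at most.

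Finally, the t test and Wilcoxon remark is minor, since pairwise use is possible.

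**Conclusion.** The concern holds for the stated rule. Testing randomised arms at baseline and adjusting when a difference appears makes the model depend on chance, and subgroup analysis is not a correction. The 40% to 54% figure rests on an assumed 10 to 15 independent tests at 5%.

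For the stratification factors and baseline outcomes, the conclusion is conditional: they are not named, and if they are omitted there is a cost in precision. The article gives no correlation, no share of variance explained by strata and no number of tests, so that cost cannot be computed from it. The tables above show assumed ranges for linear analyses only.

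Two stronger inferences are not supported. Omitting strata after stratified randomisation does not produce false positives; under balance within strata, the error runs the other way. Nor do the arm totals of 44, 36 and 32 physicians show imbalance within strata, because no per-stratum counts are given.

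This should be changed before analysis, but it does not undermine the trial.

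**What to change.** In Analysis:

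1. Keep the baseline tables descriptive. Delete the sentence that makes adjustment depend on differences being found, including its reference to subgroup analysis.
2. For each patient and parent outcome, prespecify one model of the follow-up value, of a type suited to the outcome, with arm, geographic area, practice size, the baseline value of the same outcome, and baseline age and severity. It should allow for clustering by physician, since physicians were randomised.
3. For each physician outcome, prespecify arm, geographic area, practice size and the physician's own baseline value. Patient age and severity do not belong in these models.
4. Present any other adjustment as a sensitivity analysis.
5. If a variance gain over change scores is cited, restrict it to continuous outcomes that would otherwise be analysed as change scores without baseline adjustment.

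The cost is wording only: the strata are known from randomisation, and the baseline surveys are already part of the design.
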